## Abstract

**Background:**

Worldwide, approximately 800,000 persons die by suicide every year; with rates of suicide attempts estimated to be much higher. Suicidal persons often suffer from a mental disorder but stigma, lack of available and suitable support, and insufficient information on mental health limit help seeking. The use of internet-based applications can help individuals inform themselves about mental disorders, assess the extent of their own concerns, find local treatment options, and prepare for contact with health care professionals. This project aims to develop and evaluate e-mental health interventions to improve knowledge about suicidality and to reduce stigmatization of those affected. In developing these interventions, a representative telephone survey was conducted to detect knowledge gaps and stigmatizing attitudes in the general population.

**Methods:**

First, a national representative telephone survey with *N* = 2000 participants in Germany was conducted. Second, e-mental health interventions are developed to address knowledge gaps and public stigma detected in the survey. These comprise an evidence-based health information package about suicidality, information on regional support services, a self-administered depression test—including suicidality—and an interactive online intervention including personal stories. The development is based on a trialogical exchange of experience between persons affected by suicidality, relatives of affected persons, and clinical experts. Australian researchers who developed an e-mental health intervention for individuals affected by rural suicide were invited to a workshop in order to contribute their knowledge and expertise. Third, the online intervention will be evaluated by a mixed methods design.

**Discussion:**

From representative telephone survey data, content can be developed to address specific attitudes and knowledge via the e-mental health interventions. These interventions will be easily accessed and provide an opportunity to reach people who tend not to seek professional services, prefer to inform themselves in advance and/or wish to remain anonymous. Evaluation of the online intervention will provide information on any changes in participants’ self-stigma and perceived-stigma of suicidality, and any increase in participants’ knowledge on suicidality or self-efficacy expectations.

**Trial registration:**

German Clinical Trial Register DRKS00015071 on August 6, 2018.

## Background

Worldwide, more than 800,000 people die by suicide every year [1]. Compared to other regions in the world, Europe had the highest suicide rate in 2016 (15.4 per 100,000 population). In Germany, approximately 10,000 people die by suicide every year (13.6 per 100,000 population in 2016) [2]. Rates of suicide attempts are estimated to be much higher: For each person who dies by suicide, it is estimated that more than 20 others attempt suicide [1]. Since suicide is a sensitive issue, it is difficult to quantify exact numbers of suicide attempts and suicide deaths. The World Health Organization [1] assumes that suicide is under-reported. Even in countries with good reporting systems suicide may be missclassified as another cause of death [1]. Around 90% of people dying by suicide in Western industrialised countries have been diagnosed with a mental health condition, particularly affective disorders, substance-related disorders, schizophrenia, and personality disorders [3–5].

Suicide is a complex issue with multiple contributing factors. Although many people who die by suicide experience a diagnosed mental health condition, suicidality is also influenced by situational factors, e.g. physical illness or injury, financial problems, or other life crises [1]. Effective treatment of poor mental health is impeded by stigma [6–8], lack of available and suitable support and insufficient information on mental health [9].

In terms of stigma, public, self, and perceived stigma can be distinguished. This project targets all three dimensions of stigma. Public stigma comprises stigmatizing reactions and attitudes of the general public towards members of a particular social group (for example persons with suicidal thoughts). Negative beliefs about this group (“Persons with suicidal thoughts have a weak will”) and negative emotional reactions (“I feel annoyed by that”) can lead to discriminating behaviour e.g. withholding help [10, 11]. Self-stigma implies that negative emotional reactions, or stereotypes are internalized which means affected persons apply them to themselves (“Because I had thoughts of ending my life, I have a weak will.”), which leads to lower self-esteem and self-efficacy [12]. While public stigma can be seen as a direct social jugdement, perceived stigma is the expected negative reaction of the public by an individual in response to their mental health condition. This can effect self-concept, functioning, and adequate health care utilization [7, 13, 14].

In Germany, less than half of all people experiencing a mental health condition report having used any provider or service for mental health reasons [15]. Easy access opportunities to inform individuals about their health and to build personal capacity to manage their health could help people who do not have, or want access to traditional health services.

There is evidence that a range of interventions (e.g. interventions in educational settings, or via information websites) can improve knowledge about mental disorders, and support recognition, management and prevention efforts [16]. Mental health literacy has focused on the recognition of mental illnesses, knowledge about risk factors and causes, about self-help and professional help or knowledge on prevention of mental disorders with the aim of enabling help-seeking [17, 18]. Thus, improving mental health literacy is part of the e-mental health interventions.

Due to the widespread use of modern communication technologies (in 2017, 81% of the German population were internet users [19]), new possibilities arise for improving support for people with mental health problems or other health crises. For example, the US National Institute of Mental Health has recommended the development of innovative treatment approaches that are both affordable and accessible to a large population [20]. Modern communication technologies provide this opportunity.

Recent studies report that the use of new media (e.g. the internet) can be effective in both treating and preventing mental disorders [21–25]. Internet-based applications can help people inform themselves about mental disorders, to assess the extent of their own concerns, to find local treatment options, and to prepare for contact with health care professionals. Self-help programs can significantly contribute to improve symptoms [26]. As demonstrated by the results of the OSPI-Europe suicide prevention program [27], awareness campaigns can help to reduce stigma and foster openness towards seeking and accepting professional help. A recent review on suicide prevention strategies [28] shows evidence for the effectiveness of restricting access to the means of suicide (e.g. firearms, analgesic medication), education campaigns in schools, specific psychopharmacological and psychotherapeutic approaches, and the aftercare of persons with a previous suicide attempt.

There has been limited evaluation of the effectiveness of e-mental health approaches to suicide prevention [28]. In a randomized controlled trial, unguided online self-help interventions aiming to reduce suicidal ideation showed a reduction in suicidal thoughts compared to a waitlist control group in a Dutch sample [29]. In a more recent Australian randomized controlled trial (online self-help intervention based on the Dutch program vs. attention-matched control program) no group differences in suicidal thinking were found [30].

For online interventions aiming to reduce suicide stigma, a recent study has been undertaken in Australia [31]. However, the study’s outcomes are not yet available ([32], Kennedy AJ, Brumby SA, Versace VL, Brumby-Rendell T: The ripple effect: a digital intervention to reduce suicide stigma among farming men, submitted). It is presumed that stigma is associated with higher prevalence of suicide [33]. There is some evidence for a link between self-stigma and suicidality. A recent longitudinal study shows that self-stigma impedes the lives of persons with mental disorders by increasing suicidality. Suicide prevention could be improved by interventions that reduce stigma [34, 35].

## Methods

### Study aims

This project aims to develop and evaluate e-mental health interventions in order to improve knowledge and to reduce suicide stigma. The target group are persons with suicidal thoughts or suicide attempts in the past, their relatives, and persons generally interested in the topic.

The interventions will be integrated in the evidence-based German e-mental health portal https://www.psychenet.de/ [36], established since 2011, and currently supported by the German Association for Psychiatry, Psychotherapy and Psychosomatics (DGPPN). The portal provides evidence-based health information on several mental illnesses and general topics concerning mental health, decision aids and self-tests on mental disorders (e.g. depression, somatoform disorders, eating and anxiety disorders), as well as information on the German health care system, and an awareness campaign on mental health. People affected by mental disorders and their relatives were involved in the development process. *Psychenet.de* intends to increase mental health literacy to empower users in managing mental health challenges [37, 38].

The project is focused on the following aims:*To realize a representative population survey of knowledge and attitudes towards suicidality in Germany:* Knowledge about causes, signs, support, and treatment options of suicidality as well as attitudes towards suicidal persons (stigma) will be evaluated in order to deduce knowledge gaps and stigmatizing attitudes which can be addressed by the e-mental health interventions.*To develop e-mental health interventions:* Two e-mental health interventions will be developed: (a) an extension of the existing e-mental health portal psychenet.de focused on suicidality, and (b) an interactive online intervention focused on reducing suicide stigma, which will be available on a subdomain of *psychenet.de*. Evidence-based health information about suicidality and information on regional support services for severe mental or suicidal crises will be developed for both. One item assessing suicidal thoughts will be added to the existing self-test for depressive disorders (PHQ-9 [39]) and will be uploaded on *psychenet.de*. The interactive online intervention, inspired by the Australian project *The Ripple Effect* [31, 40], will consist of reports by persons with an experience of suicide in the form of 10–20 videos (duration: 2–5 min) and written experience reports. Psychoeducative elements and strategies to deal with suicide stigma will be developed for different target groups.*To evaluate the e-mental health interventions:* For evaluating the extension of the existing e-mental health portal *psychenet.de* (a) we will use web analytics. For evaluating the online intervention (b), participants will be recruited via *psychenet.de*. In a pre-post survey, we will evaluate to what extent an interactive online intervention reduces self-stigma and perceived-stigma, improves suicide literacy, self-efficacy expectations, and affects the participants’ intention to seek help (outcome evaluation). The participants’ evaluation of the content of the online intervention (e.g. satisfaction, helpful aspects) will also be assessed immediately after completing the intervention, as well as in a follow-up survey 12–26 weeks after completing the intervention (process evaluation). While the pre-post survey will primarily collect quantitative data, the follow-up survey will provide qualitative data by semi-structured telephone interviews.

## Aim 1: representative population survey

### Study design

In April and May 2018, a cross-sectional telephone survey with *N* = 2000 persons was conducted in Germany. The survey dealt with attitudes and knowledge towards suicidality and was conducted by a professional market- and social-research institute. Time taken to do the survey was approximately 20 min.

A case vignette with signs and symptoms of a person with suicidal thoughts was presented to the participants. The vignettes systematically varied in gender (female vs. male), age (younger vs. older person) and disorder (mental disorder: depression, somatic disorder: cancer) resulting in eight different vignettes and approximately 250 respondents for each combination. The vignettes were developed by the project team and discussed with physicians, psycho-oncologists, psychotherapists, and people with lived experience. They were audio-recorded with a trained speaker to increase reliability and to counteract possible interviewer effects. The vignettes are:

#### Mental disorder (depression)

The 32−/73-year old Johanna D./Johannes D. has been feeling depressed and sad for a couple of months. Ms./Mr. D. feels useless, has the impression of doing everything wrong and has lost any interest in the things that usually brought joy to her/him. She/he doubts that her/his life has any meaning and, with increasing frequency, thinks about taking her/his own life.

#### Somatic disorder (cancer)

The 32−/73-year old Johanna D./Johannes D. has been told a couple of months ago, that she/he is suffering from cancer. Currently Ms./Mr. D. is constantly exhausted and suffers from nausea and pain. She/He is feeling hopeless and fears a progression of the disease. She/he doubts that her/his life has any meaning and, with increasing frequency, thinks about taking her/his own life.

### Study sample: inclusion and exclusion criteria

The sample consisted of adults aged 18 and older, living in private households with a landline or cell phone in Germany. In order to reach all groups of persons, telephone numbers were drawn from all registered telephone numbers at random. Ex-directory households and cell phone numbers were included via computer-generated numbers. Persons younger than 18 years or those with neither a mobile phone number nor a landline number were excluded. As this is a questionnaire in German, people who did not understand German were also excluded.

### Data collection

The population telephone survey was conducted by the market- and social-research institute USUMA which is located in Berlin. Data was collected with the aid of a computer assisted telephone interview (CATI). To get representative data for the adult residential population in Germany, the sample consisted of randomly generated mobile phone numbers and non-registered numbers as well as randomly selected registered telephone numbers. In households with more than one resident, the Kish selection grid was used to randomly select the target person [41]. This multilevel sample design ensured that in every household with multiple residents, each person had the same chance to be selected for the survey. Collected data was transferred to the University Medical Center Hamburg-Eppendorf for data analyses.

### Measures

The questionnaire asked about attitudes and knowledge concerning suicide and persons with suicidal thoughts respectively.

After having heard the vignette, participants were asked to what extent they would agree to the following statement: “I would feel and think the same as that person when being in the same situation.” Using a 4-point Likert scale ranging from 1 “strongly disagree” to 4 “strongly agree”, a continuum of self-distinction could be assessed.

Concerning mental health literacy, questions on signs of suicidal thoughts, causes of suicidality, offers of care and treatment options (availability and effectiveness) were asked.

Further, we used the short form of the Literacy of Suicide Scale (LOSS-SF) [42]. Items of the LOSS-SF consist of true and false statements about suicide and suicidal thoughts. Participants state whether they believe these statements are true or false.

In terms of measuring participants’ attitudes towards persons with suicidal thoughts, several instruments that measure stigma of mental illness were used:

The Desire for Social Distance Scale [43] assesses a person’s disposition or reluctance to socially engage with a certain group of persons. The scale contains seven items, each representing a social relationship: tenant, co-worker, neighbour, person one would recommend for a job, person of the same social circle, in-law, and child-carer. Respondents indicated on a 4-point Likert scale to what extent they would accept a person with suicidal thoughts ranging from 1 “strongly disagree” to 4 “strongly agree”.

Further, respondents were asked about their emotional reactions towards affected persons using a list of nine items representing several ways of responding to a person with suicidal thoughts. On a 4-point Likert scale coded from 1 (“strongly disagree”) to 4 (“strongly agree”), respondents stated their agreement to the statements covering the dimensions ‘anger’ (e.g. “I react angrily”), ‘fear’ (e.g. “He/she scares me”) and ‘pro-social’ reactions (e.g. “I feel sympathy”), which were yielded in former principal component analyses [44, 45].

Additionally, we used the short form of the Stigma of Suicide Scale (SOSS-SF) [46]. The SOSS-SF comprises 16 descriptors of a “typical” person who dies by suicide, covering three factors: ‘stigma’, ‘isolation/depression’, and ‘glorification/normalization’. Participants state on a 5-point Likert scale (strongly disagree, disagree, neutral, agree, strongly agree) to what extent they agree with the attributing descriptor (e.g. ‘brave’, ‘isolated’, ‘stupid’). Since the whole questionnaire in this study focused on persons with suicidal thoughts, we modified the original wording from “people who commit suicide” to “people who have suicidal thoughts”.

Additionally, we collected the socio-demographic variables age, gender, education and occupational status as well as religious denomination.

### Statistical analysis

Group differences on suicide stigma between the different vignettes are assessed. Normal distribution is tested using the Kolmogorov-Smirnov-test. Group differences in means are tested for non-parametric and categorical data using the Mann-Whitney-U-test and Chi^2^-test respectively. For parametric data, the t-test is used to compare two groups respectively to conduct an analysis of variance (ANOVA) to draw comparisons between more than two groups. Correlations between more than two variables are examined with multiple linear regression analyses. The unstandardized B-coefficient, the Beta-coefficient, significance and the explained variance (R^2^) are considered.

All analyses are conducted with the statistics software IBM SPSS 25 [47]. For all analyses, results with *p* ≤ 0.05 are considered statistically significant.

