### Statistical analysis

For pre-post comparisons (SOSS-SF, LOSS-SF, and self-efficacy expectation scores), we will use the t-test for dependent samples (all three scales are interval-scaled). Kolmogorov-Smirnov test will be used to test normal distribution. Analyses will be conducted for participants who have completed pre and post measurement of SOSS-SF, LOSS-SF, and self-efficacy expectation (“completers”). In case of single missing values, the restricted maximum likelihood-method will be applied. Age, gender and nature of suicide experience (self-afflicted, close person like a friend or family member, interested person) will be considered for subgroup and regression analyses. Participants who have started the intervention but have not completed will be compared to completers in terms of age, gender, and nature of suicide experience, provided data is available. To access the acceptance of the intervention, dropout rate will be calculated. Satisfaction with the intervention will be evaluated descriptively (mean values and standard deviations). All analyses will be conducted using the statistics program IBM SPSS 25 [47]. For all analyses α ≤ 0.05 will be considered statistically significant.

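### Aim 1 survey: a Kolmogorov-Smirnov test decides how vignettes are compared, and scores that fail it get only a two-group rank test, with no eight-vignette comparison and no interactions

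*Protocol article*

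**What the plan says.** Under Aim 1, Study design, the protocol article describes a crossed experiment within the telephone survey of N = 2000: "The vignettes systematically varied in gender (female vs. male), age (younger vs. older person) and disorder" (depression or cancer), "resulting in eight different vignettes and approximately 250 respondents for each combination".

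Under Aim 1, Statistical analysis, the purpose is stated first: "Group differences on suicide stigma between the different vignettes are assessed". The rule for choosing a method follows:

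- "Normal distribution is tested using the Kolmogorov-Smirnov-test".
- For scores judged non-normal: "Group differences in means are tested for non-parametric and categorical data using the Mann-Whitney-U-test", with the chi-squared test for categorical data.
- For scores judged normal: "For parametric data, the t-test is used to compare two groups respectively to conduct an analysis of variance (ANOVA"), the latter for more than two groups.

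The section then lists multiple linear regression for relationships among more than two variables, reporting B, Beta and R². This is not tied to the normality result. The significance threshold is 0.05 throughout.

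**The concern.** ANOVA is the only method named for comparing a score across more than two groups, and it sits only on the parametric branch. The non-parametric branch names no rank test for more than two groups and no factorial rank method. So the normality test decides whether the survey's stated comparison, between the different vignettes, has a method at all.

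The outcomes are bounded, discrete scores built from 4- and 5-point items. A goodness-of-fit test with 2000 observations will detect that discreteness whether or not it matters for comparing means. The likely result is that most stigma scores go to the branch that cannot compare eight groups, cannot examine whether the depression-versus-cancer difference varies with the age or gender of the person described, and gives no mean difference. Mann-Whitney U also does not test a difference in means, which is how the section describes its purpose.

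**Working it through.** **1. Reproduce the plan's figure.** Three two-level factors give 2 × 2 × 2 = 8 vignettes, and 2000 / 8 = 250 per vignette, as stated. Each factor level has 2000 / 2 = 1000 respondents.

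**2. Inputs from the Measures section.** A single 4-point item; social distance, 7 four-point items; emotional reactions, 9 four-point items in three dimensions; SOSS-SF, 16 five-point items in three factors. Items per dimension or factor are not given, so 3 items (emotional reactions) and 4, 8 and 16 items (SOSS-SF) are assumptions.

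**3. Critical distance of the test at 0.05.**

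- Uncorrected, 1.3581/√n: 1.3581/44.72 = 0.0304 at n = 2000; 1.3581/15.81 = 0.0859 at n = 250.
- Lilliefors, 0.895/(√n − 0.01 + 0.85/√n): 0.0200 at n = 2000; 0.0564 at n = 250.

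**4. How often normality is rejected.** There were 200 simulated samples per setting. Items came from a one-factor normal latent trait with inter-item correlation 0.2 or 0.4 (ranges below span the two), with symmetric or skewed cut-points. All of these are assumptions.

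| Score | n = 2000, Lilliefors | n = 2000, uncorrected | n = 250, Lilliefors | n = 250, uncorrected |
|---|---|---|---|---|
| 1 × 4-point, symmetric or skewed | 100% | 100% | 100% | 100% |
| 3 × 4-point, symmetric | 100% | 100% | 100% | 100% |
| 4 × 5-point, symmetric | 100% | 100% | 100% | 41.5–66% |
| 7 × 4-point, symmetric | 100% | 100% | 97–100% | 11.5–22.5% |
| 7 × 4-point, skewed | 100% | 100% | 100% | 100% |
| 8 × 5-point, symmetric | 100% | 100% | 76–84% | 1.5–2.5% |
| 8 × 5-point, skewed | 100% | 100% | 100% | 90.5–99% |
| 16 × 5-point, symmetric | 100% | 75.5–78.5% | 25–31% | 0–0.5% |
| 16 × 5-point, skewed | 100% | 100% | 99.5–100% | 43–80% |

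At n = 2000 the mean distance for the symmetric 8-item sum was 0.046 to 0.049, well above both critical values. For the symmetric 16-item total it was 0.034, only just above the uncorrected 0.0304, which explains the one exception.

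**5. What the rank branch can and cannot see.** There were 400 simulated surveys of 2000 on a symmetric 7-item, 4-point score, with effects in latent-factor SD. Mann-Whitney was applied to each factor in turn and compared with a full 2 × 2 × 2 linear model and a one-way ANOVA of the eight vignettes.

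- Disorder main effect of 0.2: Mann-Whitney on disorder 98.8%, linear model 99.5%.
- Pure gender × disorder interaction (disorder effect +0.2 for one gender, −0.2 for the other): Mann-Whitney on gender, age and disorder 4.0%, 6.5% and 4.75%, about the nominal level. The interaction term of the linear model detected it in 98%, and the eight-group ANOVA in 84.5%.
- No effect: all procedures rejected in 5.0% to 7.75%. The Monte Carlo standard error is √(0.05 × 0.95/400) = 1.1 percentage points.

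**6. Whether the gate protects anything.** ANOVA of eight groups of 250 on a 7-item score with skewness about 1.15, no true difference, 3000 runs: type I error 0.051.

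**The case against.** The strongest reply is that the section already lists multiple linear regression with no normality condition, and that model class is the remedy. This stands in part. The tool is there, so the factorial structure is not simply discarded. But the section gives regression a different job, the study of relationships among several variables, and does not say that the vignette factors or their interactions enter it. The vignette comparison is assigned to the gated tests.

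Second, all three factors have two levels, so a two-group test is available for every main effect at about 1000 against 1000. This stands, and step 5 shows that the power loss is trivial. No interaction hypothesis is stated either. What remains is the comparison across eight vignettes, the interactions that a crossed design makes available, and the effect estimates.

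Third, the section does not say whether normality is tested on the pooled sample or per vignette, or with which correction. This also stands: some longer symmetric scores would pass at 250. A reader might infer that every Likert score must fail and that ANOVA can never be reached, but the figures do not support that. The method would instead depend on an unstated choice, which is itself a reason to remove the gate.

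Two further inferences are tempting and unsupported. One is that the eight vignettes will be tested in all possible pairs at 0.05, with the resulting error inflation; the article nowhere states a pairwise procedure. The other is that the Aim 3 primary test would be switched after seeing the data. Aim 3, Statistical analysis, does say "Kolmogorov-Smirnov test will be used to test normal distribution", but it names the dependent t-test outright and attaches no consequence or fallback to that check.

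**Conclusion.** The point holds for the Aim 1 survey only. The article states a rule under which a normality test chooses the method, and one branch of that rule has no comparison of more than two groups. If the test is run on the pooled 2000, nearly all stigma scores take that branch: 100% of simulated single items and sums of 3 to 8 items, and 75.5% to 100% for a symmetric 16-item total. At about 250 per vignette the outcome ranges from almost never to always, depending on score length, skewness and the correction.

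The loss is the eight-vignette test, interactions (detected at about the nominal level by Mann-Whitney against 98% by a factorial model) and mean differences. Main effects are not lost. Nothing is gained in return, since ANOVA is valid at this size even on strongly skewed scores. The simulated rates rest on the assumed item counts, latent-trait model, inter-item correlations and cut-points given above. The Aim 3 pre-post analysis and its N = 241 are unaffected. The wording should be changed, but the trial's primary outcomes do not depend on it.

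**What to change.** In Aim 1, Statistical analysis, remove the Kolmogorov-Smirnov test as the basis for choosing a method. State that each stigma score is analysed, whatever its distribution, with one linear model (factorial ANOVA or the regression already listed) containing vignette gender, age, disorder and their interactions. Report estimated mean differences with confidence intervals based on robust standard errors. Keep Mann-Whitney U as a sensitivity analysis of the main effects, and do not describe it as a test of means.

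The cost is a few sentences. The survey data are already collected, the sample size does not change, and both model types are already named in the section. Because collection is complete, the article or its analysis plan should say when the model was fixed relative to the vignette comparisons.
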